### Trial management and quality control

An independent data monitoring committee will be formed according to the Data Monitoring Committees: Lessons, Ethics, Statistics (DAMOCLES) guidance [32] to oversee the efficacy and safety throughout the trial and will consist of a statistician, an audiologist, an otologist, and an expert in clinical studies.

### Sample size, data collection, and statistical methods

The calculations will be analyzed by the PASS Power Analysis Software (NCSS; Kaysville, UT, USA). According to the power calculations, we assume an *α* of 0.05 and a power of 0.8. The sample size estimation was calculated by the PASS software using the Test for Two Proportions. Based on our clinical experience, feasibility, and the previously reported study [33], with the incidence of a 20% improvement in THI set to 75%, the calculated sample size is 56 participants with a 1:1 allocation. The lost-to-follow-up rate is estimated to be 10%, so we plan to enroll 31 participants in each group.

The data collection will use the FTRS collection platform and the hospital information system to record the answers to the questionnaires and the outcomes of the clinical testing. The questionnaires are designed with inbuilt check-and-skip rules after pretesting by study staff to minimize data-entry errors. The data will be centralized, classified, and protected in long-term storage in the data repository.

Our analysis conforms to the intention-to-treat principle [34]. Descriptive statistics will be used in this study, and IBM SPSS will be used to calculate the means, 95% confidence intervals, ranges, and frequencies. Means ± standard deviations will be used to express the data, and one-way analysis of variance (ANOVA) will be used to compare multiple means. Tinnitus scores from the THI, HADS, and AIS questionnaires will be compared between the HA and WLC groups using Student’s *t*-test with adjustment for multiple comparisons. The chi-square test will be used to test numerical data, and correlations among the study variables will be tested using Pearson’s coefficient. For non-normally distributed variables, the Mann–Whitney *U*-test will be used for between-group comparisons. Adjusted effect size estimates and 95% confidence intervals will be used to determine the statistical significance. A linear model will be used for the analysis with age, gender, and baseline value as covariates. Meanwhile, the effect of treatment will be additionally evaluated by a linear mixed model [35] (if applicable) to account for repeated measures of each outcome. When the proportion of missing values exceeds the predefined threshold of 5%, sensitivity analyses will be conducted using multiple imputation [36] to evaluate the potential impact of the remaining missing values. All of the patient information will be presented anonymously and confidentially throughout the analysis process.

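### The protocol gives two incompatible rules for judging the single primary outcome, THI (a multiplicity-corrected t-test shared with secondary scales, and a baseline-adjusted linear model), and does not say which decides

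*Protocol article*

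**What the plan says.** All of this is in the protocol article, mainly under Sample size, data collection, and statistical methods.

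- **Rule A.** "Tinnitus scores from the THI, HADS, and AIS questionnaires will be compared between the HA and WLC groups" by Student's t-test, corrected for multiple comparisons. Neither the procedure nor the family is named. Mann–Whitney replaces the t-test for non-normal variables.
- **Rule B.** "Adjusted effect size estimates and 95% confidence intervals will be used to determine the statistical significance". The next sentence reads: "A linear model will be used for the analysis with age, gender, and baseline value as covariates".
- **Further analyses.** A linear mixed model for the repeated measures is described as additional and conditional. Multiple imputation is planned as a sensitivity analysis when more than 5% of values are missing.
- **Outcome.** The abstract gives the primary outcome as THI, continuous, at 6 months. The Primary outcome measure section gives it as the change in THI.
- **Sizing.** The calculation takes an alpha "of 0.05 and a power of 0.8". "The sample size estimation was calculated by the PASS software using the Test for Two Proportions", "with the incidence of a 20% improvement in THI set to 75" per cent. This gives 56 participants, with 62 to be enrolled.
- **Randomisation.** It is stratified by baseline THI, at or below 36 against above 36 (Recruitments and randomization).

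**The concern.** A multiplicity-corrected t-test and an uncorrected 95% confidence interval from a covariate-adjusted model can disagree on the same data. The text gives both a claim to settle significance and ranks neither. This is a conflict between stated rules, so it does not depend on a detail that an unseen SAP might supply.

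Two things are at stake. First, the trial's main conclusion could depend on which sentence is followed once results are known. Second, the t-test route may be the weaker one. It puts the primary outcome in a corrected set with HADS and AIS although the sample size allowed for no correction. If it is applied to the 6-month score, it also leaves out the baseline THI that the trial considered important enough to stratify on.

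**Working it through.** **1. The plan's own figure.** The 56 cannot be reproduced from the printed inputs, because no control-arm response rate is given. Taking 75% as the hearing-aid rate, a two-sided two-proportion test without continuity correction needs 28 per group when the control rate is 38.1% to 38.6%. With continuity correction the range is 34.4% to 35.1%. The full alpha of 0.05 is used, with no allowance for several scales.

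**2. Setting for the power comparison.** The protocol gives no THI standard deviation, mean difference or baseline-to-follow-up correlation r, so the figures below are illustrative. With n = 28 per group and 54 degrees of freedom, choose the standardised difference d that gives 80% power for a two-sided t-test at 0.05. By the noncentral t distribution d = 0.762, and the noncentrality is d × √(n/2) = 0.762 × √14 = 2.85.

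**3. Cost of sharing alpha (Bonferroni assumed).** THI, HADS and AIS make three tests. Counting HADS-A and HADS-D separately makes four.

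| Tests | Alpha for THI | Critical t | Power |
|---|---|---|---|
| 1 | 0.05 | 2.005 | 80.0% |
| 3 | 0.05/3 = 0.0167 | 2.471 | 64.9% |
| 4 | 0.05/4 = 0.0125 | 2.584 | 60.7% |

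Restoring 80% would take 38 or 40 per group instead of 28. On the proportion scale (75% against an assumed 38%, 28 per group), power goes from 82% to 67% and 62%, so the pattern does not depend on using a t-test. Holm would lose less. A fixed sequence with THI first would lose nothing.

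**4. Use of baseline.** Let σ² be the variance of the 6-month score, equal at baseline. The outcome variance is then

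- 6-month score: σ²
- change: 2(1 − r)σ²
- score adjusted for baseline: (1 − r²)σ²

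Dividing d = 0.762 by the square root of each factor gives, at two-sided 0.05 with no multiplicity correction:

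| Assumed r | t-test on score | t-test on change | Baseline-adjusted |
|---|---|---|---|
| 0.4 | 80% | 72% (factor 1.2) | 86% (factor 0.84) |
| 0.5 | 80% | 80% (factor 1.0) | 90% (factor 0.75) |
| 0.6 | 80% | 88% (factor 0.8) | 94% (factor 0.64) |

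The adjusted model is ahead at each r. Its lead over the score t-test is about 6, 10 and 14 points, and over the change t-test about 14, 10 and 6 points.

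**5. Score or change.** Write the adjusted model as Y = a + b·group + c·B, where B is baseline THI and Y is 6-month THI. Subtracting B from both sides gives Y − B = a + b·group + (c − 1)·B. The group coefficient b is identical, so a baseline-adjusted model removes the discrepancy between the abstract and the outcome section. A t-test does not.

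**The case against.** The strongest reply is that the text can be read coherently: the sentence on adjusted estimates makes the baseline-adjusted linear model decisive, and the t-test is a simple unadjusted comparison. On that reading the power gain in step 4 is already in the plan and the multiplicity correction does not touch the deciding result. The reading is fair but the document does not state it. The t-test sentence names THI, applies a correction and is not labelled secondary or descriptive. What stands of the reply is that the t-test cannot be called the primary analysis as a matter of fact.

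A reader might infer more than the text supports in five places.

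- **That the primary test definitely pays for the secondary scales.** The correction is unnamed, and a fixed sequence starting with THI would cost it nothing.
- **That baseline THI is definitely discarded.** This holds only for a t-test on the 6-month score. A t-test on change uses baseline, though less efficiently than adjustment.
- **That the mixed model is a third competing rule.** The protocol describes it as additional.
- **That participants without 6-month THI will be dropped despite "Our analysis conforms to the intention-to-treat principle".** "The lost-to-follow-up rate is estimated to be 10" per cent, about 6 of 62, and a t-test or linear model on observed 6-month data alone would omit them. But the protocol does not say they will be excluded. That loss would trigger the planned multiple imputation, and the mixed model could use 3-month THI.
- **That type I error is inflated.** In a null simulation (28 per group, r from 0.4 to 0.7), taking the smaller p-value of the score t-test and the adjusted model, each at 0.05, gave about 7% to 9%. Nothing in the protocol says the result will be chosen that way, and a corrected t-test would add less.

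**Conclusion.** The concern holds as an unresolved conflict: two stated rules can give different answers for THI, and neither is named as deciding. That conclusion needs no assumptions beyond the text.

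The size of the consequence is conditional. The fall from 80% to about 65% or 61% needs the t-test to decide and Bonferroni to be applied to three or four tests. The gain to about 86%, 90% or 94% needs the comparator to be a t-test on the 6-month score and r to be 0.4, 0.5 or 0.6. Both rest on a d chosen to give 80% power, because the trial was sized on proportions. Within those limits, the baseline-adjusted model at the full 0.05 is the better choice. The point should be settled before any unblinded THI comparison.

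**What to change.** Name one primary analysis: the linear model already planned, for the 6-month THI difference between groups, with baseline THI, age and gender as covariates, reported with its 95% confidence interval. The mixed model using 3- and 6-month THI with the same covariates is an acceptable alternative, and preferring one over the other is largely a matter of taste. Test THI at 0.05, state the sidedness (two-sided is assumed above), and apply no correction for the secondary scales. Any allowance for the two planned interim analyses is a separate question.

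Confine the multiplicity correction to the secondary scales and name the procedure and family. Label the t-test, Mann–Whitney and whichever model is not primary as supportive, and keep multiple imputation as a sensitivity analysis of the primary model. Describe the primary outcome in the same way in the abstract and the outcome section.

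The cost is a few sentences of wording. Every model is already in the protocol, and neither data collection nor sample size changes.

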**Methods and design:**

The present study is a prospective, single-center, outcome assessor and data analyst-blinded, randomized, controlled trial. Eligible participants will be recruited and randomly allocated into the HA intervention group and the waiting list control group at a ratio of 1:1. The primary outcome is to evaluate the severity of tinnitus using the Tinnitus Handicap Inventory as a continuous variable at 6 months from randomization. Secondary outcome measures include changes in hearing status and mental states. The trial will last 6 months, with follow-up visits at 3 months and 6 months.

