### Recruitments and randomization

This study will be conducted in the outpatient ENT department of the Eye and ENT Hospital of Fudan University in Shanghai, China. Our institution is a specialized hospital focused on otorhinolaryngology. In addition, we developed an app—the Fudan Tinnitus Relieving System (FTRS)—that will be used for the management, treatment, data collection, and efficacy analysis of tinnitus patients. The participants will be primarily included in the study after being diagnosed with probable chronic subjective tinnitus with bothersome symptoms after the screening procedure. Screening for hearing and tinnitus testing typically consists of PTA, speech audiometry test, and distortion product otoacoustic emissions (DPOAE) along with several widely accepted tinnitus questionnaires such as the THI for tinnitus severity, the visual analog scale (VAS) for tinnitus loudness, and the HADS and AIS-8 for mental health status. The entire test will generally take a mean time of approximately 30 min. Participants will scan the two-dimensional code we supply via their smartphones and will fill out the questionnaires online through the FTRS.

Interested patients will be directed to the research room to receive the necessary details of the study. Before participation, informed and written consent will be obtained from all participants by the principal investigator. The randomization will be stratified by the THI score (≤ 36 or > 36 [18]) based on the baseline assessment in order to avoid an uneven distribution of patients. An independent researcher who is not involved in the recruitment process or outcome measurement will generate a random sequence (http://www.random.org) to randomly assign the participants in a 1:1 allocation to treatment using HAs or to the WLC group. The randomization sequence will be concealed in sequentially numbered sealed and opaque envelopes. Participants will then be notified via telephone or email which group they are allocated to by the staff member who kept the randomization sequence file and who will not participate in any subsequent assessment of the patients. Data analysts, study coordinators, and outcome assessors will remain unaware of the group assignments until the primary analyses are completed.

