### Outcome measurements and follow-ups

#### Primary outcome measure

The primary outcome measure is the change in the THI score [20]. The THI is a self-administered test including 25 questions that determine the degree of function, emotional status, and adverse reactions in the patient with tinnitus. The respondent answers the questions on a 3-point Likert scale with responses of “no” (0 points), “sometimes” (2 points), and “yes” (4 points) yielding an overall score ranging from 0 to 100. The following criteria are used to determine effectiveness [21]: curative = THI score decreased to less than 16 points; significantly effective = THI score decreased by more than 17 points; and ineffective = THI score decreased by less than 17 points, or even increased. The THI has been demonstrated to be a well-known, reliable, and valid clinical tool when evaluating the severity of tinnitus and for assessing the performance of HAs [22]. The proposed study will use the THI Chinese (Mandarin) version [23].

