### Blinding

For this intervention, it is not feasible to blind participants and clinicians regarding the treatment condition owing to the nature of the clinical treatment modalities. However, by separating the intervention and analysis staff, independent investigators in our hospital will perform all follow-up evaluations blinded to the group allocation. We will also attempt to minimize assessment bias and achieve the maximum trial blinding through the following measures: (1) both the data collectors and the assessors will be trained to achieve high interrater reliability, (2) participants and data collectors will be masked as far as possible to block size when collecting the data, and (3) the outcome data assessor will be blinded from randomization until the statistical analyses of the experimental outcomes are completed.

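### Allocation is stratified by baseline THI, yet unstratified tests of THI, HADS and AIS stand unranked beside the adjusted model; those tests are conservative, most clearly for THI

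*Protocol article*

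**What the plan says.** Under Recruitments and randomization, the Protocol article states: "The randomization will be stratified by the THI score (≤ 36 or > 36 [18]) based on the baseline assessment". Allocation is 1:1. The Blinding section adds that "participants and data collectors will be masked as far as possible to block size when collecting the data", which implies permuted blocks, although no block size is given.

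The primary outcome appears in two forms. The abstract assesses tinnitus severity "using the Tinnitus Handicap Inventory as a continuous variable at 6 months from randomization"; under Primary outcome measure, "The primary outcome measure is the change in the THI score".

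The section on sample size, data collection and statistical methods describes the between-group analyses as follows:

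- Student's t-test for THI, HADS and AIS, with a multiplicity adjustment attached to it.
- Mann–Whitney for non-normal variables.
- Chi-square, for what the text calls numerical data.
- A statement that adjusted effect estimates with 95% intervals decide significance.
- A linear model "with age, gender, and baseline value as covariates".
- A linear mixed model as an additional analysis, if applicable.

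No test or model names the randomisation stratum.

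**The concern.** Blocked allocation within strata of a prognostic variable makes the arms more alike than simple randomisation would, so the true variance of the arm difference falls. A test that ignores the strata still charges for the between-stratum variance. Its standard error is too large, its real type I error is below 5%, and power is lost.

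Baseline THI is very likely to predict later THI, and with 28 evaluable patients per arm there is little power to spare. The text attaches the t-test directly to the primary score and two key secondary scores, and gives that test the multiplicity adjustment. An analyst following the text could therefore report the conservative test as the main result.

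**Working it through.** **Inputs from the document.** Strata at THI 36; 1:1 allocation; 56 patients before loss, so 28 per arm; α = 0.05, taken as two-sided because sidedness is not stated. The article gives no standard error or power for these tests. Its one figure, 56, comes from a two-proportion calculation that states one rate (75%) and no comparator, so it cannot be reproduced. It would fit a comparator rate of about 38–39% (two-sided, 27 to 29 per arm). It is used here only as the sample size.

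**Assumptions, not in the document.** Correlation ρ between baseline and 6-month THI of 0.4, 0.6 or 0.8; effect 0.6 SD; bivariate normal scores; strata cut at the median; balance within strata.

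**Variance explained by the stratum.**

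- 6-month score: R² = ρ² × 0.3989² / 0.25 = 0.637ρ².
- Change score: the variance is 2(1 − ρ) and the covariance with baseline is −(1 − ρ), so R² = 0.637(1 − ρ)² / [2(1 − ρ)] = 0.318(1 − ρ).

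The t-test standard error exceeds the true one by k = 1/√(1 − R²). The true level is 2·P(T₅₄ > 2.005k).

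| ρ | 0.4 | 0.6 | 0.8 |
|---|---|---|---|
| 6-month THI: R² | 0.102 | 0.229 | 0.407 |
| k | 1.055 | 1.139 | 1.299 |
| true level | 3.9% | 2.6% | 1.2% |
| THI change: R² | 0.191 | 0.127 | 0.064 |
| k | 1.112 | 1.070 | 1.033 |
| true level | 3.0% | 3.6% | 4.3% |

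**Power on 6-month THI.** The standardised effect is 0.6/√(2/28) = 2.245. Normal approximations:

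- t-test, Φ[(2.245 − 2.005)k]: 60 / 61 / 62%.
- Stratum in the model, Φ(2.245k − 2.006): 64 / 71 / 82%.
- Continuous baseline THI in the model, Φ(2.245/√(1 − ρ²) − 2.006): 67 / 79 / 96%.

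Simulation with 28 per arm (8,000 null and 4,000 alternative trials per correlation) agrees. The t-test level is 3.7 / 2.4 / 1.3%. Power is 61 / 60 / 62% for the t-test, 65 / 71 / 82% with the stratum and 68 / 78 / 96% with continuous baseline. With permuted blocks of 4 and the cut at 36 (assumed mean 40, SD 20), the t-test level is 3.5 / 2.9 / 1.1% and Mann–Whitney 3.3 / 2.9 / 0.9%, with Mann–Whitney power 58 / 58 / 60%. For the article's curative category (THI below 16), chi-square power is 31 / 32 / 30%, against 33 / 37 / 40% for Cochran–Mantel–Haenszel.

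**The stated linear model for THI.** Setting: 56 patients, blocks of 4, SD 20, difference 15 points, ρ = 0.3 / 0.5 / 0.7, 4,000 runs each.

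- Model SE over true SE: 0.98 / 1.00 / 1.00. Type I error: 5.8 / 4.7 / 5.0%.
- Power when the stratum is added: 80.0 to 79.2%, 87.3 to 87.1%, 96.0 to 95.7%. There is no gain, and none even with an extra 5- or 10-point outcome step at the cut.
- In the same setting, t-test power is 78.6 / 81.7 / 83.6% on the 6-month score and 66.4 / 81.0 / 95.0% on change.

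**Secondary outcomes.** Assumptions: own-baseline correlation 0.5; baseline correlated 0.5 or 0.7 with THI; direct stratum effect 0 or 0.3 SD; treatment effect 0.75 SD.

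- t-test on the final score: SE ratio under the null 1.02–1.08, level 3.4–4.2%.
- t-test on change: SE ratio 1.00–1.03, level 4.5–5.4%, so essentially correct.
- Own-baseline model, power without and with the stratum: 86.3 and 86.1%, 87.0 and 87.3%, 86.5 and 86.4%, 86.2 and 86.6%. Further runs under similar assumptions showed a change of about one point.

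**The case against.** The strongest reply is that the covariate-adjusted model already decides. The sentence that adjusted estimates determine significance comes immediately before the sentence specifying the model, and that is its natural reading. If so, the t-tests are supportive and the primary result loses nothing. This stands as a limit on the point. It does not remove it: the text never ranks the t-test below the model, and it ties the multiplicity adjustment to the t-test.

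Second, a reader might infer from the covariate list that the linear model also has standard errors too wide for the design. The document does not support this. For THI, the listed baseline value is the variable from which the strata are cut, in finer form, and the calculations show correct standard errors. Nor does leaving THI out of the HADS, AIS or hearing-outcome models cost material power.

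Third, the error is in the safe direction: no inflated false positives and no bias in the estimate. This stands.

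Fourth, stratum terms and stratified test versions are details often left to an analysis plan, which is not shown. That holds for the mere absence of a stratum term. It does not hold for tests that the article itself specifies without ranking.

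**Conclusion.** The point holds for the unadjusted t, Mann–Whitney and chi-square comparisons, and for the failure to say clearly that the adjusted model governs. For 6-month THI, the t-test runs at a true level of about 4% down to 1%, with about 61% power where the planned model would have 68–96%. For THI change the level is about 3–4%. For HADS and AIS the effect of ignoring the stratum is small on final scores and close to nil on change.

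Not all of the power gap comes from ignoring the stratum. That part is the step from about 61% to 65 / 71 / 82%; the rest comes from using baseline THI in full, which the stated model already does.

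These sizes rest on assumed correlations, effect sizes and THI distribution, and on blocks within strata, which the Blinding section implies but does not detail. The conclusion does not extend to the stated linear model for THI, and for secondary-outcome models the case for including the stratum is analysing as randomised, not power.

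**What to change.** In the statistical methods section:

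- State that between-group inference for THI, HADS, AIS and the other outcomes rests on the baseline-adjusted linear or mixed models.
- Include the THI stratum (≤ 36 / > 36), or continuous baseline THI, in the secondary-outcome models. The THI model needs no further term.
- Present unadjusted t-tests as descriptive only, and move the multiplicity adjustment to the model-based comparisons.
- Where a rank or categorical test is kept, use the version stratified by THI: van Elteren in place of Mann–Whitney, Cochran–Mantel–Haenszel in place of chi-square.

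The cost is wording and at most one degree of freedom per model. Baseline THI is already collected, and neither the sample size nor the conduct of the trial changes.

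### The main THI comparisons can use only patients with an observed 6-month score; the named mixed model should carry the main estimate and multiple imputation should be unconditional

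*Protocol article*

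**What the plan says.** All the analysis statements are in the Protocol article, section Sample size, data collection, and statistical methods, unless noted.

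- Principle: "Our analysis conforms to the intention-to-treat principle".
- Primary endpoint (Abstract, Methods and design): the "Tinnitus Handicap Inventory as a continuous variable at 6 months from randomization".
- Unadjusted comparison: the questionnaire scores, THI among them, "will be compared between the HA and WLC groups using Student’s *t*-test with adjustment for multiple comparisons". The Mann–Whitney test replaces it for non-normal variables.
- Adjusted comparison: "A linear model will be used for the analysis with age, gender, and baseline value as covariates".
- Repeated measures: "the effect of treatment will be additionally evaluated by a linear mixed model", and this only where it is found applicable.
- Missing data: "When the proportion of missing values exceeds the predefined threshold of 5%, sensitivity analyses will be conducted using multiple imputation".
- Expected loss and enrolment: "The lost-to-follow-up rate is estimated to be 10%, so we plan to enroll 31 participants in each group".

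The section Time points schedules THI at 3 months as well as at 6 months.

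**The concern.** A t-test, a Mann–Whitney test or a linear model on the 6-month THI takes in only patients for whom that score exists. The one imputation method named is reserved for sensitivity analyses, so nothing in the article brings a patient without a 6-month score into the main result. A patient who attended at 3 months and then stopped would contribute nothing to it, although that score predicts the missing one better than baseline alone is likely to.

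Loss that depends on arm or on benefit is plausible here. Participants are not blinded (Blinding), the primary outcome is self-administered (Primary outcome measure), and only the hearing-aid arm carries a daily wearing requirement (Intervention). If the patients lost differ from those retained, and the pattern differs by arm, a comparison of observed scores shifts the estimated THI difference. The article foresees the loss, but gives its two better-suited methods an optional or conditional role.

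**Working it through.** **Inputs from the article.** 56 participants before loss (28 per arm), 10% expected loss, 31 per arm enrolled (62 in total), 5% trigger, THI at 3 and 6 months.

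**Assumed inputs.** THI SD of 20; a gap of 10 to 20 THI points between lost and retained patients; arm-specific loss rates as shown below. The article gives none of these.

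**1. The plan's own enrolment figure.** 56 × 1.10 = 61.6, rounded up to 62, or 31 per arm. This reproduces the stated figure. Dividing by 0.9 instead gives 63 in total (or 32 per arm), a difference too small to matter for this point.

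**2. Patients outside the main comparison.** 62 × 0.10 = 6.2 lost; 62 − 6.2 = 55.8 with a 6-month score. So the t-test and linear model would rest on about 56 of 62 randomised patients.

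**3. The 5% trigger.** Applied to the 6-month THI, 5% of 62 is 3.1, so the trigger is passed once 4 or more scores are missing. If each patient has an independent 10% chance of loss, the number lost is binomial (62, 0.10):

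- P(0) + P(1) + P(2) + P(3) = 0.0015 + 0.0100 + 0.0340 + 0.0755 = 0.121
- P(4 or more) = 1 − 0.121 = 0.879

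Multiple imputation would therefore probably be run. In the remaining 12% or so of cases it would not be.

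**4. Size of a possible bias.** Let g be the mean THI of lost patients minus that of retained patients, and p the fraction lost in an arm. The full-arm mean is the retained mean plus p × g, so the retained mean is too low by p × g. If g is the same in both arms, the difference between arms is biased by (p_HA − p_WLC) × g, in favour of the arm with more loss when g is positive.

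| Loss, HA v WLC | Gap g | Bias in THI points |
|---|---|---|
| 15% v 5% | 10 to 20, both arms | 0.10 × 10 to 0.10 × 20 = 1 to 2 |
| 20% v 0% (extreme) | 10 to 20 | 0.20 × 10 to 0.20 × 20 = 2 to 4 |
| 10% v 10% | 10 to 20, HA arm only | 0.10 × 10 to 0.10 × 20 = 1 to 2 |
| 10% v 10% | same in both arms | 0 |

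**5. Scale.** The unadjusted standard error with 28 per arm is 20 × √(2/28) = 5.35. A bias of 1 to 2 points is 1/5.35 to 2/5.35, or about 0.2 to 0.4 of a standard error. The extreme 4 points is about 0.75 of one. In the adjusted linear model, only the part of the gap not explained by age, gender and baseline THI would matter.

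**The case against.** Several points on the other side are sound.

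- **Exclusion is inferred.** Nowhere does the article say that patients without a 6-month score are removed, and its reference to the missing values that remain leaves a little room for earlier handling. The inference rests on the tests named and on imputation being kept for sensitivity analyses.
- **Intention-to-treat may mean analysis by allocated arm.** A reader might infer that the plan contradicts itself. The text does not establish that: nothing regroups patients by treatment received or removes non-adherent users. What remains is incomplete handling of missing outcomes under that label.
- **The trigger is not a source of bias.** A reader might infer that it blocks imputation. On the plan's own loss rate it will probably be met, and it withholds imputation only when 3 or fewer of 62 scores are missing, where the effect is smallest. It is untidy, no more.
- **The sensitivity analysis is not blind to the problem.** Imputation that uses arm, baseline and 3-month THI can recover the part of any shift that those data predict. Only the remainder escapes.
- **Arm-dependent loss is a possibility, not a finding.** The plan requires 6-month availability and excludes those unwilling to use aids daily (Participants). It collects questionnaires by app and keeps contact by messaging and telephone (Participant withdrawal). Waiting-list patients have a reason to stay, since they receive the intervention afterwards (Intervention).

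These points limit the weight of the concern. They do not remove it: the method that keeps partly followed patients is still additional and conditional, and no main THI estimate is defined that includes them.

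**Conclusion.** The point holds as a worthwhile, inexpensive improvement. As written, the main THI comparisons would omit about 6 of 62 randomised patients at the expected loss, including any who gave a 3-month THI, while the methods that could use those patients have a conditional role.

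The likely effect is modest: 1 to 2 points under the assumed gap and a 10-percentage-point difference in loss, and below one standard error even in the extreme case. These sizes depend wholly on the assumed SD, gaps and loss rates, and the 0.88 depends on independent losses at 10%. The documents do not support a claim that the primary result will be materially biased.

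A reader might also count the lack of an analysis under departures from missing at random as an error. It is not: an article commonly leaves that detail to the full protocol or analysis plan, which is not shown.

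**What to change.** 1. Make the main THI estimate the 6-month arm difference from the linear mixed model already named. Include baseline THI, age, gender and the 3- and 6-month scores, for all randomised patients with any follow-up. Remove its applicability condition for THI. The t-test, Mann–Whitney test and linear model can stay as supporting analyses.
2. Delete the 5% trigger. Run multiple imputation regardless of the missing percentage, on all 62 randomised patients, using arm, baseline THI and 3-month THI. This also brings in patients with neither follow-up score, whom the mixed model in step 1 does not cover.
3. Optionally, add an arm-specific delta-adjusted version, for example 0 to 20 THI points worse for lost hearing-aid patients, to show how far the result depends on missing at random.

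The cost is revised wording and a few model runs, with no new patients, visits or measurements. The downside is that the main estimate relies on a missing-at-random assumption, which should be stated; step 3 would examine it. The change should be fixed before allocation is unblinded.
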